
### Sample size

To determine the sample size, the methodological work of Bujang and Adnan [18] was followed. This work provides guidance for estimating the minimum sample size required in a screening or diagnostic study to achieve the desired sensitivity and specificity with adequate power and a controlled level of type I error. Based on the literature review, the level of sensitivity for the biomarkers under study ranges between 52 and 81%, while the specificity ranges between 52 and 86%. After a follow-up of about 2.5 years, the incidence of AD in a cohort of individuals with MCI was observed to range from 29 to 46% [19, 20]. Based on this data and utilising the tables provided by Bujang and Adnan, a minimum sample size of 388 individuals with MCI is needed assuming an expected incidence of AD of 40% after a 3-year follow-up period, a sensitivity value of 80% for an individual biomarker (working hypothesis), a power ≥ 80% and a *p*-value lower than 5%. Additionally, applying the formula described by Buderer [21] which incorporates the event frequency into the sample size calculation, it was verified that 400 evaluated individuals would ensure an acceptable level of precision (the half-width of the 95% CI) between 4 and 7.5% for both sensitivity and specificity (Table 2). Assuming a dropout rate of 20%, a total sample of 500 individuals with MCI has been determined.

**Table 2 Tab2:** Level of precision^a^ on the estimates of sensitivity and specificity (for a range of values) corresponding to a sample size of 400, according to an incidence of AD ranging from 27 to 40%

Incidence	Sensitivity			Specificity		
	**80%**	**85%**	**90%**	**80%**	**85%**	**90%**
***N***** = 400**						
**27%**	7.5%	6.7%	5.7%	4.6%	4.1%	3.4%
**35%**	6.6%	5.9%	5.0%	4.9%	4.3%	3.6%
**40%**	6.2%	5.5%	4.6%	5.1%	4.5%	3.8%

^a^Formula proposed by Buderer was applied

The primary objective of this study is to develop a prediction model including biomarkers in addition to clinical variables. Following the practical guidance provided by Riley et al. [22] to calculate the number of events needed for developing a multivariable prediction model, and assuming an expected C-index of 0.8 [23] which corresponds to an apparent Cox-Snell *R*^2^ of 0.31, and considering an overall incidence rate of 16% (based on an average follow-up of 2.5 years), we have determined that the number of events required per predictor parameter is 9.5. Consequently, the planned sample is deemed sufficient to include up to 17 candidate predictors.

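### The 9.5 events per parameter and the ceiling of 17 predictors treat an R² labelled apparent as if it were optimism-adjusted; if the label is right, the ceiling is about 14

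*SAP article*

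**What the plan says.** The calculation for the prediction model is the last paragraph of the Sample size section of the SAP article, below Table 2. It proceeds by "assuming an expected C-index of 0.8", "which corresponds to an apparent Cox-Snell *R*^2^ of 0.31", and by "considering an overall incidence rate of 16% (based on an average follow-up of 2.5 years". From these it reports that "the number of events required per predictor parameter is 9.5", and so "the planned sample is deemed sufficient to include up to 17 candidate predictors".

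The paragraph gives no formula, no target shrinkage and no number of events. It does not mention adjusting R² for optimism. It also does not say whether the planned sample means the evaluable or the enrolled number. Both numbers appear earlier in the section: "400 evaluated individuals would ensure an acceptable level of precision" and "Assuming a dropout rate of 20%, a total sample of 500 individuals with MCI has been determined". The same section assumes a 40% incidence of AD at three years. A shrinkage value of 0.90 appears only in the Internal validation section, as the mark above which overfitting counts as small.

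**The concern.** The criterion that yields events per parameter contains a term that turns an optimism-adjusted R² back into an apparent one. An R² that is already apparent should not pass through that term, because it is then inflated a second time and the requirement comes out too low. The plan calls its R² apparent, yet its result is the one obtained by treating it as adjusted. Label and figure cannot both be right.

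What depends on this is the ceiling on candidate parameters, which is the only numerical limit on model size set at the design stage. The ceiling also has little slack: it rests on 40% incidence, the highest of the three rows in Table 2, and the Discussion reports that the enrolment target was missed.

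**Working it through.** **Inputs**
- From the Sample size section: R² = 0.31 (labelled apparent), rate 0.16, mean follow-up 2.5 years, 400 evaluable participants, 40% incidence.
- Assumed: target shrinkage S = 0.90. It is not stated for this calculation, but it is the value that reproduces the plan's figure and it matches the mark in Internal validation.
- Inferred: 400 × 0.40 = 160 events.

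**Criterion.** Expected shrinkage for p parameters in n participants is S = 1 + p / (n · ln(1 − R²app)). Since R²adj = S · R²app, the version that takes an adjusted value is

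n/p = 1 / [(S − 1) · ln(1 − R²adj/S)].

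**1. Reproducing the plan's 9.5.** Enter 0.31 as R²adj:
- 0.31/0.90 = 0.344 and ln(1 − 0.344) = −0.422
- n/p = 1/(0.1 × 0.422) = 23.68
- events per parameter = 23.68 × 0.16 × 2.5 = 9.47, which rounds to 9.5
- 160/9.47 = 16.89, which rounds to 17

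The other settings tried do not give 9.5:

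| Change | Events per parameter |
|---|---|
| S = 0.85 | 5.9 |
| S = 0.95 | 20.3 |
| 16% read as a cumulative proportion | 3.8 |
| 3 years instead of 2.5 | 11.4 |
| R² first multiplied by 0.90 | 10.8 |

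So 0.31 was used without adjustment, and the 16% must be a rate per person-year.

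**2. Using 0.31 as an apparent value, same target.**
- ln(1 − 0.31) = −0.371
- n/p = 1/(0.1 × 0.371) = 26.95
- events per parameter = 26.95 × 0.40 = 10.78
- 160/10.78 = 14.8, so 14 whole parameters
- 17 parameters would need 17 × 26.95 = 458.1, that is 459 evaluable participants

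This is identical to entering R²adj = 0.90 × 0.31 = 0.279 in the formula of step 1. An adjustment factor of 0.90 is therefore the value consistent with a 0.90 target.

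**3. Sensitivity to the adjustment factor** (no factor is given in the document):

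| Factor | R²adj | Events per parameter | Parameters from 160 events |
|---|---|---|---|
| 0.95 | 0.295 | 10.1 | 15 |
| 0.90 | 0.279 | 10.8 | 14 |
| 0.85 | 0.264 | 11.5 | 13 |

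**4. Cost of keeping 17.** With R²app = 0.31 and n = 400, S = 1 − 17/(400 × 0.371) = 0.885.

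**The case against.** The strongest reply is that the C-index of 0.8 comes from a cited source and may already have been corrected for optimism or validated externally. Then 0.31 is an adjusted value, *apparent* is a slip of wording, and 9.5 is right. The document cannot exclude this, so the correction has to be conditional. What remains is that the sentence is inconsistent as printed.

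The event count is also an inference. Read against all 500 enrolled, 200 events would support 21 parameters at 9.47 and 18 at 10.78. However, only the 400 basis leads to the plan's own 17, so that is almost certainly what was used.

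Two stronger readings are tempting and not supported:
- A reader might infer a plain arithmetic error, because 160/9.5 = 16.8 gives 16 whole parameters and not 17. That is ordinary rounding. Seventeen parameters need 403 participants against 400, and with 0.31 taken as adjusted the expected shrinkage is 0.899.
- A reader might infer that the ceiling is the plan's only guard against overfitting. It is not. Internal validation specifies 500 bootstrap samples with the stepwise selection repeated in each, a corrected c-index and shrunken coefficients. Sensitivity analysis adds LASSO with tenfold cross-validation.

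**Conclusion.** The stated 9.5 and 17 do not follow from an R² that the plan itself calls apparent. If that label is correct, the requirement is about 10.8 events per parameter and the ceiling about 14. If the C-index was already optimism-corrected, the figures stand and the label is wrong. The documents do not say which.

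The effect is modest: expected shrinkage of about 0.885 against 0.90 at 17 parameters, in a plan that measures and corrects overfitting later. This does not invalidate the model. It makes the stated capacity of the sample optimistic by about three parameters on the plan's own label. The conclusion rests on a target of 0.90, on 160 events from 400 evaluable participants, and on reading 16% as a rate per person-year.

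**What to change.** In the Sample size section, state the target shrinkage, the assumed number of events with the sample it refers to, and that 16% is a rate per person-year. Then do one of the following:
- If 0.31 is apparent, restate the result as about 10.8 events per parameter and at most 14 candidate parameters. Express the limit in parameters, the unit in which the events requirement is given.
- If the C-index of 0.8 was already optimism-corrected, say so, replace the word *apparent* with *optimism-adjusted*, and keep 9.5.

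Because enrolment fell short of 500, as the Discussion reports, add that the ceiling will be recomputed from the observed number of conversions before the final model is fitted.

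The cost is SAP wording and, in the first case, a less favourable stated ceiling. No data collection or analysis method changes.

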### Statistical analysis method

All the analysis will be conducted on patients with the baseline assessment of biomarkers available; consequently, patients without biomarker assessment will be excluded from the primary analysis.

To exclude selection bias, a comparison of baseline characteristics of individuals not included in the analysis due to incomplete biomarkers assessment and those included in the analysis will be performed.

A multivariable predictive model of conversion to AD will be developed including biomarkers, socio-demographic and clinical predictors. The evaluation of biomarkers for MMSE, DFR, CSF parameters and MRI measures will be conducted considering the continuous form and the categorical form applying validated cut-offs.

For the MMSE [24], a cut-off of 24 (< 24) for the age- and sex-corrected score will be used, as indicated in the literature [25]. For the correction of the crude score, Measso et al. [26] will be used for individuals aged ≤ 64, and Magni et al. [25] will be used for those aged > 64. Regarding the DFR, a test result will be classified as abnormal if the age-adjusted score is ≤ 6.31 [27].

For MRI, measurements of the right and left hippocampus are considered for each technique, ACM-Adaboost and Freesurfer, and atrophy is defined below the 5th percentile according to the age-specific thresholds defined for individuals aged 56–90 years, as published [12]. For individuals aged 50–55 years, the cut-offs are extrapolated from the 5th percentile function (see Additional file 2). Right and left hippocampal atrophy measured with the two techniques will be analysed separately.

For CSF biomarkers, p-tau, t-tau, Aβ1-42, Aβ_1-42/1–40_ ratio and Aβ_1-42_ /p-tau ratio will be evaluated separately. The cut-offs used for each biomarker are reported in Table 3 along with the literature references [28–31]. For the EEG, the classification of results into normal or abnormal based on the SW values will be performed by the expert centre using a machine learning (ML) method based on fine Gaussian support vector machine. This ML classification model has been trained on external data including both healthy individuals and individuals with AD [32] and will be applied to the study cohort. The FDG-PET result will be categorised as either positive or negative by the evaluators at the expert centre based on the methodology previously described [10, 11]. In the case of FDG-PET positivity, it will also be specified whether it is indicative of an AD-like form or other forms of dementia. The APOE-e4 genotype will be classified as none, one (heterozygosis), or both alleles (homozygosis) (see Table 3 and Additional file 3 for details of the cut-offs and literature references).

**Table 3 Tab3:** Reference value for identifying abnormal values by biomarkers

Biomarker	Reference value for categorisation	Literature and notes
**MMSE**	Age- and sex-adjusted score < 24	Applied correction factors from Measso et al. [26] for age ≤ 64 and Magni et al. [25] for age > 64
**DFR**	Age-adjusted score ≤ 6.31	Frasson et al. 2011 [27]
**Hippocampal volume**	< 5° percentile of the normative population	De Francesco et al. 2021 [12]; see Additional file 3

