### Missing data

To contain the number of missing data and patient dropout, telephone contact with individuals who missed scheduled visits, or their caregivers, was planned offering the option of a remote visit if attendance was not feasible. No missing data will be accepted in the evaluation of biomarkers; therefore, it is required that all participants have a full evaluation of the biomarkers under study. A high level of completeness is expected for the main baseline characteristics, especially for age, sex and level of education. At least 80% of completeness will be required to include predictive factors in the analysis and the multiple imputation techniques by chained equations will be applied for dealing with missing data. Missing values for continuous normally distributed data will be imputed using linear regression, while the predictive mean matching method will be applied for not normally distributed data. Logistic regression will be used for binary data and ordinal logistic for ordered categorical data [43]. All predictors, including socio-demographic and clinical variables and biomarkers, will be considered potential variables for the imputation model. The outcome variable will be included in the imputation model adding the censoring indicator and the cumulative baseline hazard function estimated with the Nelson–Aalen method. For each variable with missing data to be imputed, candidate variables for inclusion in the imputation model will be selected based on their association with the missingness indicator. Associations will be assessed using *t*-test for continuous variables and chi-square test for categorical variables, with a *p*-value threshold of 0.05. If the frequency of missing data is less than 5% for each selected predictive variable, the main analysis will be conducted using only one imputed value generated according to the approach described above using the predictive mean imputation with 5 nearest neighbours to preserve variance and avoid the inflation of associations among the variable and predictors. A complete case analysis will be performed on this imputed dataset.

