## Discussion

To our knowledge, the INTERCEPTOR study represents the first publicly funded study to evaluate, through a harmonisation process among specialised centres distributed throughout the Italian territory, a wide set of biomarkers aimed at predicting the conversion from MCI to AD based over an adequate period of follow-up. The strength of this study lies in the inclusion of a broad range of biomarkers and the standardised and homogeneous collection of these biomarkers. Substantial efforts have been made to standardise biomarker acquisition and analysis, with specialised centres providing expertise in risk diagnosis classification [8]. The study has encountered challenges posed by the COVID-19 pandemic, primarily evident in the recruitment slowdown. The COVID-19 pandemic occurred when the study was in the recruitment phase. For patient recruitment, participants needed to undergo multiple visits for clinical assessment and biomarker acquisition, including at clinical centres distinct from the recruitment centre. The pandemic limited access to certain services necessary for clinical visits and biomarker acquisition. The timeline for scheduled visits has been impacted, leading to deviations from the protocol, which will be documented and appropriately addressed. Despite implementing mitigation actions aimed at ensuring the completion of the INTERCEPTOR study, such as extending the recruitment period and introducing remote visits, we were not able to reach the targeted sample size. Although the initial goal of enrolling 500 individuals with MCI was not met, the final sample size is anticipated to provide estimates of accuracy measures with sufficient precision and to enable the development of a predictive model incorporating demographical and clinical information alongside biomarkers. The model will undergo internal validation, enhancing its reliability. Nevertheless, one major limitation of this study is the lack of external validation, which is crucial to assess the generalizability and robustness of the model. However, once the model is defined, a comparison will be made with existing prognostic models for conversion from MCI to AD available in the literature, and the feasibility of conducting an external validation using data provided by other studies will be evaluated. Furthermore, it is important to note that certain methodological decisions, such as handling non-linearity and categorisation of biomarkers, were not strictly guided by the best evidence but were made to prioritise the clinical interpretability and applicability of the model. This highlights a trade-off between model performance and practical utility in clinical settings. The decision to represent the identified predictive model in the form of a nomogram aims to facilitate its interpretability and applicability with the final goal of assisting clinicians in assessing eligibility for prescribing upcoming new treatments proposed for dementia.

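### Imputation covariates are screened on association with missingness, and participants with an incomplete biomarker set enter no analysis: a risk of modest coefficient bias, lost events and unexamined selection

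*SAP article*

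**What the plan says.** Two rules are involved.

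**Who is analysed.** Statistical analysis method opens with "All the analysis will be conducted on patients with the baseline assessment of biomarkers available" and adds that "patients without biomarker assessment will be excluded from the primary analysis". The next paragraph describes the people left out as "individuals not included in the analysis due to incomplete biomarkers assessment". Missing data states: "No missing data will be accepted in the evaluation of biomarkers; therefore, it is required that all participants have a full evaluation". The safeguard offered is a comparison of included and excluded people, introduced as "To exclude selection bias, a comparison of baseline characteristics of individuals not included".

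**How other predictors are imputed.** Missing data plans multiple imputation by chained equations for predictors that are at least 80% complete. All predictors and biomarkers are potential members of the imputation model, but "candidate variables for inclusion in the imputation model will be selected based on their association with the missingness indicator", using t-tests or chi-square tests at p<0.05. The outcome (censoring indicator and Nelson-Aalen cumulative hazard) is included without passing this screen. If every predictor has less than 5% missing, a single imputed value is used, generated by the same approach.

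Sensitivity analysis varies the selection method, repeats a complete-case analysis and adds a competing-risk model. None of these brings back participants with an incomplete biomarker set.

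**The concern.** An imputation model should contain every variable of the analysis model. If a covariate is omitted, the imputed values are drawn as though it were unrelated to the incomplete predictor once the outcome is known, and this distorts the coefficients. Association with missingness is a good reason to add an auxiliary variable. It is not a reason to drop a member of the analysis model. Under the stated rule even age and sex, which are forced into the final model, can be dropped from an imputation model. Those coefficients feed the stepwise selection and the nomogram.

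The exclusion rule has a different cost. Each person removed for one missing biomarker takes an event or a non-event out of a model whose candidate count was set on the full evaluated sample. If completing all tests is related to prognosis, the analysed set is selected. A comparison of observed baseline characteristics can show some of that selection, but a null result cannot rule out the rest.

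**Working it through.** **1. The plan's own figures (Sample size)**

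- Inputs: Cox-Snell R² 0.31; incidence rate 16% with 2.5 years' average follow-up; 400 evaluated; 20% dropout. A target shrinkage of 0.90 is assumed, because the section does not state one.
- Participants per parameter: 1/[(0.90 − 1) × ln(1 − 0.31/0.90)] = 23.68.
- Event fraction: 0.16 × 2.5 = 0.40. Events per parameter: 23.68 × 0.40 = 9.47, matching the stated 9.5.
- Events: 400 × 0.40 = 160. Candidates: 160/9.5 = 16.8, matching the stated 17.
- Enrolment: 400/0.80 = 500, as stated.

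The figure of 17 uses all 400 evaluated participants and leaves no margin for further exclusions.

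**2. Further exclusion for an incomplete biomarker set**

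The plan gives no rate, so a range is assumed, with exclusion unrelated to conversion. The half-width is 1.96 × √[0.8 × 0.2/(N × 0.27)], the widest case in Table 2.

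| Excluded | N | Events | Candidates at 9.5 | Half-width |
|---|---|---|---|---|
| 0% | 400 | 160 | 16.8 | 7.5% |
| 5% | 380 | 152 | 16.0 | 7.7% |
| 10% | 360 | 144 | 15.2 | 8.0% |
| 20% | 320 | 128 | 13.5 | 8.4% |

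To place the range: if CSF, MRI, FDG-PET, EEG and APOE were each missing independently in 1% to 5%, complete sets would be 0.99⁵ = 95.1% to 0.95⁵ = 77.4%. Missingness clustered in the same people would exclude fewer.

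**3. What the missingness screen lets through**

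- If values are missing purely by chance, about 95% of covariates fail a 5% test, however strongly they correlate with the incomplete predictor.
- With 5% of 400 missing (20 against 380), a true difference of 0.3 SD gives a z of 0.3 × √(20 × 380/400) = 1.31. The power is Φ(1.31 − 1.96), about 26%.

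**4. Effect on coefficients (simulation, covariate correlation 0.6 assumed, values missing completely at random, outcome kept in the imputation model)**

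- Logistic model, n = 4000, true values 0.60 and 0.60. With the covariate omitted, estimates were 0.650 and 0.646 at 20% missing (about +8%) and 0.610 and 0.613 at 5% missing (about +2%). With it included they were 0.603 and 0.599, and 0.597 and 0.603.
- Cox model, N = 400, about 155 events, true values 0.70 and 0.70, 20% missing. Omitting the covariate moved its own coefficient from 0.713 (full data) to 0.745, or +4.5%. Including it gave 0.712, but the imputed variable's coefficient fell to 0.660, against 0.700 on full data.

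**5. Complete-case Cox estimates under different mechanisms (same Cox setting, 20% setting)**

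- Missing at random chance: 0.692 and 0.721, against 0.700 and 0.713 on full data.
- Missing by an observed covariate: 0.716 and 0.703, against 0.710 and 0.708. Events fell from about 155 to 102.
- Missing linked to early conversion: 0.750 and 0.738, against 0.719 and 0.705, or +4% to +5%.

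**The case against.** A complete biomarker set is a design requirement: Predictors says every participant must undergo all tests within 60 days, and the exclusion criteria already remove people with contraindications to MRI or lumbar puncture. Much of any selection towards fitter people therefore arises at eligibility, where imputation cannot help. A common complete set is also a defensible primary choice when biomarkers are to be compared with one another. Using each marker's own available cases, or making imputation primary, would trade that away and complicate the stepwise selection repeated in 500 bootstrap samples. This part stands, and it is why the complete set should stay primary.

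Some stronger readings are tempting but not supported.

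- A reader might infer that the imputation models contain nothing but variables associated with missingness. They do not: the outcome is always in.
- A reader might infer that coefficients will be biased. Complete-case Cox estimates were materially off only when missingness depended on the outcome given the covariates. The shift from the imputation rule in the Cox setting was about 0.03 on a standard error of about 0.10.
- A reader might take "The pandemic limited access to certain services necessary for clinical visits and biomarker acquisition" as evidence that many enrolled participants lack biomarkers. In the Discussion that sentence follows one about visits needed for recruitment, and the main effect named is slower recruitment. Incompleteness is plausible, but no rate is given.
- The 400 are called evaluated. Whether that already means biomarker-evaluated is unclear, so reading the 20% allowance as dropout alone is an interpretation.

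What the objection leaves untouched is that the covariate screen is wrong in principle, that the plan itself expects some people to be excluded for incomplete biomarkers, and that no analysis shows what difference they make.

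**Conclusion.** Both parts hold as risks, and both are modest in size.

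The imputation rule can drop analysis-model covariates that correlate strongly with the incomplete predictor. Under an assumed correlation of 0.6, the resulting shift is about 4-8% at 20% missing, the most the completeness rule allows, and about 2% at 5%. It depends on the correlations and on the amount missing. Including all covariates does not make imputation exact in a Cox model: the imputed variable's own coefficient was about 6% low (0.660 against 0.700) in the one Cox setting examined at 20% missing.

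Excluding people with an incomplete biomarker set, with no analysis that retains them, lowers the supported candidates from 17 to about 16 at 5% further exclusion and 13.5 at 20%. This assumes 40% incidence, exclusion unrelated to conversion, and an exclusion rate the plan does not give. Selection bias is possible and is not shown to be present. The baseline comparison cannot settle the question either way.

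**What to change.** - **Missing data:** put all candidate predictors and biomarkers of the analysis model, the event indicator and the Nelson-Aalen estimate in every imputation model, including the single-imputation route. Use the tests against the missingness indicator only to add auxiliary variables.
- **Statistical analysis method and Sensitivity analysis:** keep the complete-biomarker set as the primary analysis. Add a sensitivity analysis that refits the final model with partly missing biomarkers imputed by chained equations, and report the number excluded and the events among them.
- **Statistical analysis method:** state that the comparison of included and excluded participants is made to describe possible selection, not to exclude bias.

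The first and third changes are wording. The second adds some analysis work and assumes that biomarkers are missing at random given the variables in the imputation model. Because it refits the final model only, the bootstrapped selection need not be repeated within it.
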